## Abstract

**Background:**

Alcoholic liver disease is the leading cause of cirrhosis worldwide. Due to an increase in alcohol overuse, alcoholic liver disease has become an increased burden on health care systems. Abstinence from alcohol remains the cornerstone of alcoholic liver disease treatment; however, this approach is hampered by frequent relapse and lack of specific therapy for treating advanced cases of liver disease. In the present study, we hypothesized that gut microbiota drive the development of liver fibrosis and that modulation of gut microbiota with the gut-selective, nonabsorbable antibiotic rifaximin attenuates alcoholic liver fibrosis.

**Methods/design:**

Our double-blind, placebo-controlled trial will include 136 participants with biopsy-verified alcoholic fibrosis (Ishak liver fibrosis score of 1–4). Participants are randomized 1:1 to receive placebo or 550 mg of rifaximin twice daily for 18 months. A liver biopsy will be performed at the end of the treatment period to evaluate the effect of drug treatment on liver fibrosis. Stool, urine, and saliva specimens will be collected before treatment begins, at 1 month, and at the end of the treatment period. Fecal samples are used for microbiome deep sequencing. Changes in microbiome composition are compared before and after the trial medication period and linked to changes in liver fibrosis.

**Discussion:**

This is the first clinical trial to evaluate the effect of gut microbiota on liver fibrosis in humans. If gut microbiota are an important promoter of alcoholic liver disease, current results may open new therapeutic avenues and revolutionize the current understanding of chronic liver diseases.

**Trial registration:**

EudraCT, 2014–001856-51. Registered on 16 August 2014.

**Electronic supplementary material:**

The online version of this article (10.1186/s13063-018-2523-9) contains supplementary material, which is available to authorized users.

## Background

Alcohol consumption is the leading cause of liver cirrhosis in humans, and mortality from alcoholic liver disease compared to other common chronic diseases is on the rise [1, 2]. Unfortunately, research related to alcoholic liver disease is relatively underfunded and subject to limited interest from pharmaceutical companies; therefore, no new therapeutic interventions have been developed in the last few decades [3]. Furthermore, patients with this disease are often stigmatized, present a relatively high socioeconomic burden, and are a key societal challenge. Excessive alcohol consumption stimulates extracellular matrix production from hepatic stellate cells, which accumulates as liver fibrosis and replaces normal liver tissue. Although the liver is able to recover to some extent, sustained misuse of alcohol over several years can lead to progressive accumulation of liver fibrosis and eventually cirrhosis.

Due to its anatomical position, the liver is the first organ to encounter bacteria and bacterial products from the gut via portal venous blood. During alcoholic liver disease, intestinal microbiota change qualitatively and quantitatively in favor of a community with increased invasive potential, and the gut barrier is compromised [4]. As a consequence, an increased load of bacterial products are transported to the liver, where they activate Toll-like receptors, leading to proinflammatory gene expression and fibrogenesis [5]. This cross-talk between intestinal microbiota and the liver constitutes a gut-liver axis, which has been increasingly recognized as a key mechanism in the progression of alcoholic liver disease and pathogenesis of liver-related complications [6, 7].

### Study rationale

Modulation of gut microbiota using broad-spectrum antibiotics is currently being used in clinical hepatology to protect against complications associated with advanced liver diseases, such as bacterial translocation, spontaneous bacterial peritonitis, and recurrent episodes of hepatic encephalopathy [7]. Rifaximin, a nonabsorbable derivative of rifampicin, is currently being used to help treat traveler’s diarrhea and prevent recurrent episodes of hepatic encephalopathy in advanced liver disease [8]. Rifaximin exerts a broad-spectrum bactericidal effect against gastrointestinal bacteria by binding to the β-subunit of bacterial DNA-dependent RNA polymerase [9]. Previous studies have shown that rifaximin has a modest impact on the composition of gut microbiota. However, these studies were done in patients with end-stage liver disease using a 16S ribosomal RNA gene sequencing with limited microbiota sequencing depth [10, 11]. To date, there have been no studies evaluating the possible antifibrotic effect of modulating human gut microbiota with antibiotics. However, an increasing body of evidence from animal studies, including models of alcoholic liver disease, supports this notion [12, 13]. Due to its ability to selectively target gut microbiota with minimal systemic uptake [14] and its documented efficacy against complications related to advanced liver disease [8], as well as liver fibrosis in a preclinical model [13], we chose to use rifaximin to modulate gut microbiota in the present clinical trial.

### Study aim and hypothesis

We hypothesize that human gut microbiota and their metabolites are major promoters of fibrosis in alcoholic liver disease. Therefore, modulation of gut microbiota by rifaximin can attenuate or halt disease progression by decreasing the amount of profibrotic signals from gut microbiota reaching the liver.

## Methods/design

The present biopsy-controlled, double-blind study will include a total of 136 patients randomized 1:1 to receive a 550-mg tablet of rifaximin or placebo twice daily for 18 months. Randomization is being performed in blocks of four, with stratification according to the Metavir fibrosis score from initial liver biopsies and whether or not participants abstained from alcohol for 6 months prior to study onset. Participants are each assigned a consecutively numbered three-digit identification number in the trial. Each identification number is by chance allocated to either placebo or rifaximin. The randomization list is generated electronically by a central computer stored at the pharmacy at Odense University Hospital (Odense, Denmark); only authorized pharmacy personnel know the randomization code. Sponsors, investigators, nurses, laboratory assistants, and/or personnel involved in trial participant care have no knowledge of the randomization. Sealed, opaque envelopes with randomization keys for each participant are being kept at Odense University Hospital. Sponsors and investigators have access to the coded envelopes at all times in case unblinding is necessary. Placebo tablets will be similar in size, shape, and weight to the rifaximin tablet to secure concealment. Pre- and post-treatment biopsies are assessed together in a blinded manner by one expert pathologist. Fecal samples are collected at home and frozen immediately in a home freezer. They are transported to the clinic in ice where they are stored at –80 °C. Samples are processed for shotgun metagenomics sequencing of the gut microbiota using the recommended procedures by the International Human Microbiome Standards Consortium [15]. Saliva samples are collected at the clinic in two tubes. One tube is frozen to –80 °C immediately. The other is stored at +5 °C for 3 h before freezing to –80 °C. Microbial DNA extraction is performed with a Macherey-Nagel NucleoSpin Kit, and 16S ribosomal RNA gene sequencing of the oral microbiota is performed by amplifying the V4 hypervariable region using standard procedures [16]. Urine samples are collected to detect the presence or absence of ethyl glucuronide, a marker of alcohol consumption. For further information, see the populated Standard Protocol Items: Recommendations for Interventional Trials (SPIRIT) checklist in Additional file 1.

### Primary outcome measure

The primary outcome measure is the proportion of patients with an improvement in their liver biopsy Ishak (fibrosis) score greater than or equal to 1.

### Secondary outcome measures

The secondary outcome measures are as follows:Markers of fibrosis: collagen proportionate area, enhanced liver fibrosis score, Pro-C3, and hydroxyproline levelMarkers of matrix remodeling: tissue inhibitor of metalloproteinase 1, matrix metallopeptidase 2, and profibrotic cytokines (transforming growth factor β1, platelet-derived growth factor β, and connective tissue growth factor)Proinflammatory cytokines: tumor necrosis factor α, monocyte chemoattractant protein 1, and cluster of differentiation 163Liver stiffness assessed by transient and shear wave elastographyChanges in the composition of the gut microbiota assessed by shotgun metagenomics sequencingQuality of life assessed by the Short Form (36) Health Survey and Chronic Liver Disease QuestionnaireNutritional status assessed by weight and hand grip strength

### Recruitment and enrollment of participants

Participants are being recruited from an ongoing observational study (*Liver Disease in Alcohol Overusing Patients*) at the department of Gastroenterology and Hepatology, in which liver biopsies were taken from 400 patients with alcohol overuse (defined as the use of ≥ 24 g alcohol/day for women and ≥ 36 g alcohol/day for men; approved by regional committees on health research ethics for southern Denmark, project ID S-20120071). Among these, a subset of 136 patients will be enrolled in the current study if they comply with the inclusion and exclusion criteria outlined below.

#### Inclusion criteria

The inclusion criteria are as follows:Women of child-bearing age and potential should use safe contraception and provide a negative pregnancy test during the study period.Patients with a liver fibrosis Ishak score of 1–4.

#### Exclusion criteria

The exclusion criteria are as follows:Patients with a known allergy to rifaximinPatients whom the investigator judges will not be or are not compliant with the trial treatment protocolPatients who received antibiotic treatment of any kind 4 weeks prior to study onset

#### Study withdrawal

Patients will be withdrawn from the study for the following reasons:If blinding is repealedIf the patient undergoes treatment with another antibiotic for more than 4 consecutive weeks or four times during the study periodIf the trial participant withdraws written consentIf the investigator judges that withdrawal is in the participant’s best interest

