#### Study dropouts

Trial participants will be classified as dropouts if they meet either of the following criteria:The trial participant ingests less than 75% of the planned treatment.The trial participant does not attend planned visits, despite contact by telephone, letter, or mail.

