### Sample size calculation

According to a previous trial, alcoholic liver fibrosis was calculated to regress in 27% of patients, remain unchanged in 57%, and progress in 16% over a 2-year period when patients with hepatitis C were excluded [17]. Therefore, we estimated the natural history of regression to be approximately 14% during an 18-month period for our study population. The smallest relevant difference is considered to be a 25% absolute increase in the percentage of patients who regress by 1 point or more in their histological score. If the risk of performing type 1 and type 2 errors is set to 5% and 20%, respectively, then 136 patients are needed when one performs a power calculation using a two-sided test; this includes a dropout rate of 20%. Both intent-to-treat and per protocol analyses will be performed.

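### Unblinding and prolonged or repeated use of other antibiotics take patients out of the study itself, which puts their 18-month biopsy at risk and undermines the promised intention-to-treat analysis

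*Protocol article*

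**What the plan says.** Four parts of the protocol article bear on this point.

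- **Study withdrawal.** The list is introduced by "Patients will be withdrawn from the study for the following reasons". Its four reasons are broken blinding, another antibiotic beyond a stated limit (over 4 weeks in a row, or four times), withdrawn consent, and the investigator's judgement of the participant's best interest. The section speaks of leaving the study, not of stopping trial medication or leaving an analysis set.
- **Study dropouts.** A separate section classes participants as dropouts if they miss planned visits or if "The trial participant ingests less than 75% of the planned treatment".
- **Primary outcome and its timing.** The outcome is "the proportion of patients with an improvement in their liver biopsy Ishak (fibrosis) score greater than or equal to 1". The Abstract (Methods/design) gives the timing: "A liver biopsy will be performed at the end of the treatment period to evaluate the effect of drug treatment on liver fibrosis". A patient without the second biopsy has no observed primary outcome.
- **Sample size calculation.** The section states "Both intent-to-treat and per protocol analyses will be performed" and includes a 20% dropout rate in the total of 136.

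The article does not say whether a withdrawn patient still has the 18-month biopsy.

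**The concern.** An intention-to-treat analysis is strongest when the outcome is sought from every randomised patient, whatever happens after randomisation. Broken blinding and heavy use of other antibiotics are reasons to leave someone out of a per-protocol set. Neither is in itself a reason not to measure the outcome. The withdrawal rule applies per-protocol logic to follow-up.

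The patients affected may differ from the rest. The Study rationale section describes rifaximin as a broad-spectrum antibacterial, so the need for other antibiotics could differ by arm. Patients with long or repeated infections may also have a different liver prognosis. These are plausible mechanisms; the article gives no rates for them.

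If the biopsies are not taken, the arms with observed outcomes are no longer the randomised arms. An analysis plan can say how missing values are handled, but it cannot supply a biopsy that was never sought.

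**Working it through.** **1. The plan's own figure.** Inputs, all from Sample size calculation:

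- control regression p1 = 0.14 ("we estimated the natural history of regression to be approximately 14% during an 18-month period")
- target difference 0.25 ("The smallest relevant difference is considered to be a 25% absolute increase in the percentage of patients who regress by 1 point or more"), so p2 = 0.39
- error rates ("If the risk of performing type 1 and type 2 errors is set to 5% and 20%, respectively"), two-sided
- 20% dropout

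For two proportions, n = [1.96·√(2·p̄(1−p̄)) + 0.8416·√(p1(1−p1)+p2(1−p2))]² / 0.25², with p̄ = 0.265.

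- √(2·0.265·0.735) = 0.624 and √(0.1204+0.2379) = 0.599.
- n = (1.223+0.504)²/0.0625 = 47.7, so 48 per arm.
- With the continuity correction, (47.7/4)·[1+√(1+4/(47.7·0.25))]² = 55.4, so 56 per arm.
- 56 × 1.2 = 67.2, so 68 per arm, or **136 in total**. This matches the plan. (Dividing by 0.8 instead gives 70 per arm, or 140.)

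The sample size is not in dispute here.

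**2. How far missing biopsies can move the result.** Let m be the fraction missing in each arm, assumed equal. Let the observed rates among those biopsied be 14% and 39%.

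- Worst case: every missing placebo patient improved and no missing rifaximin patient did. Difference = 0.39(1−m) − [0.14(1−m)+m] = 0.25(1−m) − m.
- Best case: the reverse. Difference = 0.25(1−m) + m.

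| m (assumed) | Patients per arm (68·m) | Worst | Best |
|---|---|---|---|
| 5% | 3.4 | 0.2375 − 0.05 = 18.8 points | 0.2375 + 0.05 = 28.8 points |
| 10% | 6.8 | 0.225 − 0.10 = 12.5 points | 0.225 + 0.10 = 32.5 points |
| 20% | 13.6 | 0.20 − 0.20 = 0 points | 0.20 + 0.20 = 40 points |

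The article does not say how many patients would meet the two triggers. The 20% row borrows the whole dropout allowance.

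**3. Analysing everyone with missing counted as no improvement.** If the missing patients would in truth have regressed at 14% and 39%, the expected difference shrinks to 0.25(1−m): 23.75, 22.5 and 20 points for the three rows. Power without continuity correction, with 68 per arm randomised:

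| Situation | Power |
|---|---|
| All biopsies obtained | 91.9% |
| 20% missing, biopsied patients only | 85.0% |
| 20% missing, counted as no improvement | 82.2% |

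Under equal loss, then, power falls only moderately. The more serious exposure is bias, if loss is related to arm or prognosis.

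**The case against.** The strongest reply is that the loss of the biopsy is inferred. The article is condensed, the full protocol is not shown, and follow-up after withdrawal or the handling of missing biopsies may be set out there or in an analysis plan. This stands as far as it goes: no sentence says that a withdrawn patient has no biopsy. But being withdrawn from a study ordinarily means no further study procedures, nothing in the article says otherwise, and the point challenges a rule that is printed, not a detail left out.

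A reader might infer that intention-to-treat becomes impossible, or that the trial will in effect analyse completers only. The article supports neither. It commits to intention-to-treat, and all 136 can be analysed with missing biopsies imputed or counted as no improvement. If withdrawn patients in fact never regress, the latter carries no bias. The difficulty is that such assumptions cannot be tested without the biopsies.

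A reader might also infer that any antibiotic course removes a patient. It does not: one, two or three ordinary courses stay below the limit. Nor does the article show that unblinding differs by arm. The earlier rifaximin trial described under Drug information had similar moderate and serious adverse events in both arms.

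The exclusion criterion on compliance might be read as a further route out after randomisation. It stands among the enrolment criteria, and low intake during the trial is dealt with under Study dropouts, so that reading is strained. Best-interest withdrawal protects participants and is not criticised here.

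**Conclusion.** The point holds in a limited form. For two of the four listed reasons, broken blinding and long or repeated use of other antibiotics, the rule takes patients out of the study when taking them out of the per-protocol set would suffice. Read as written, it puts their primary outcome at risk and undermines the intention-to-treat analysis without making it impossible.

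The size is uncertain because the number affected is not given. The bounds rest on equal loss per arm and on observed rates equal to the planning rates. A reader might take 0 to 40 points as the likely damage. It is not: it charges the plan's total dropout allowance to these two triggers, although low intake, missed visits and withdrawn consent also lead to dropout or loss. At 5% missing, the worst case still leaves 18.8 of the 25 points. The direction of any bias is unknown.

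**What to change.** For broken blinding and for antibiotic use beyond the stated limit, replace withdrawal from the study with wording such as: recorded as a protocol deviation and excluded from the per-protocol set only; the patient remains in follow-up, and the already planned 18-month biopsy and samples are still sought, with consent. State that these patients stay in the intention-to-treat set. Leave withdrawal of consent, the investigator's best-interest provision and all decisions on trial drug as they are.

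The cost is a short amendment and an instruction to study staff. No procedure is added to the plan. The one real downside is that some patients who would otherwise have left are still asked to have the planned biopsy, with the risks set out under Risks and disadvantages for participants. By the Trial status section, 66 patients had been enrolled and 25 had completed by August 2017, so 136 − 66 = 70 were still to be enrolled and most biopsies were still ahead.

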#### Study dropouts

Trial participants will be classified as dropouts if they meet either of the following criteria:The trial participant ingests less than 75% of the planned treatment.The trial participant does not attend planned visits, despite contact by telephone, letter, or mail.

### Sample size calculation

According to a previous trial, alcoholic liver fibrosis was calculated to regress in 27% of patients, remain unchanged in 57%, and progress in 16% over a 2-year period when patients with hepatitis C were excluded [17]. Therefore, we estimated the natural history of regression to be approximately 14% during an 18-month period for our study population. The smallest relevant difference is considered to be a 25% absolute increase in the percentage of patients who regress by 1 point or more in their histological score. If the risk of performing type 1 and type 2 errors is set to 5% and 20%, respectively, then 136 patients are needed when one performs a power calculation using a two-sided test; this includes a dropout rate of 20%. Both intent-to-treat and per protocol analyses will be performed.

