### Ethics

Currently there are no known effective drugs to treat fibrotic liver disease, and the effects of rifaximin remain unclear. Hence, no patient will be withheld medication with proved efficacy by participating in this trial. All patients should continue their regularly prescribed medications during the trial. Patients receiving placebo are unlikely to experience any improvements in their disease or symptoms due to the treatment *per se*. However, it is necessary to treat half of the patients with placebo in order to ascribe observed effects to rifaximin with certainty. All patients are at risk for disease progression and will benefit from close follow-up and early detection of advanced liver disease by undergoing a liver biopsy. During the trial, participants will be encouraged to reduce their alcohol consumption. As suggested by a previous study, many patients who overuse alcohol included in clinical trials on alcoholic liver disease stop drinking or reduce their alcohol consumption, causing spontaneous improvement of their liver disease symptoms [20]. Overall, we believe the benefits of participating in this trial outnumber the risks, and we also believe it to be ethically safe. Informed consent is obtained from all participants.

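### The 14% control regression rate does not follow from the cited 27% over 2 years, and the paper does not show which rate and test produced 136 patients

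*Protocol article*

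**What the plan says.** All the planning figures are in the protocol article, Methods/design, Sample size calculation. The source figure is that "alcoholic liver fibrosis was calculated to regress in 27% of patients, remain unchanged in 57%, and progress in 16% over a 2-year period", with hepatitis C patients excluded. The next sentence gives the planning rate: "Therefore, we estimated the natural history of regression to be approximately 14% during an 18-month period for our study population". The effect is set as follows: "The smallest relevant difference is considered to be a 25% absolute increase in the percentage of patients who regress by 1 point or more". This makes the target 14% + 25% = 39%. The error rates are 5% and 20%, and the conclusion is "then 136 patients are needed when one performs a power calculation using a two-sided test; this includes a dropout rate of 20" per cent. The section names neither the test, nor any continuity correction, nor the way dropout was added.

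The primary outcome (Primary outcome measure) is the proportion of patients whose Ishak score improves by at least 1 point, so 14% is the planning rate for the placebo arm on the primary endpoint.

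**The concern.** The word *Therefore* presents 14% as a consequence of the 27% just cited. The only change that the text names is the shorter period, 18 months instead of 24. That change removes about a quarter of the rate, whereas 14% is about half of 27%. The hepatitis C exclusion is already in the 27%, so it cannot explain the drop.

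Two things are at stake. First, the control rate is the benchmark against which the placebo arm will be read. A placebo rate of 20% or a little more would look surprising beside 14%, although it is what the cited figure predicts for 18 months. Second, for a fixed 25-point difference in this range, a lower control rate means smaller variance and higher power. If 136 was derived at 14%, the stated 80% need not hold at 20% to 21%.

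**Working it through.** **1. Scaling the cited rate to 18 months**

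- Linear: 0.27 × 18/24 = 20.25%.
- Constant hazard: 1 − 0.73^0.75 = 21.0%.
- For comparison, at 12 months: 0.27 × 0.5 = 13.5% (linear) or 1 − 0.73^0.5 = 14.6% (constant hazard).

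So 14% is close to the 12-month figure. The document does not say that it arose that way.

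**2. Reproducing 136 from the printed inputs (14% against 39%, two-sided 5%, 80% power)**

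Pooled-variance formula per arm: n = [1.960·√(2·p̄(1−p̄)) + 0.842·√(p1(1−p1) + p2(1−p2))]² / 0.25², with p̄ = 0.265.

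- First term: 1.960 × √(2 × 0.265 × 0.735) = 1.223.
- Second term: 0.842 × √(0.1204 + 0.2379) = 0.504.
- n = (1.223 + 0.504)² / 0.0625 = 47.7, so 48 per arm, 96 in all; 96/0.8 = 120. This is not 136.
- With continuity correction: n' = (n/4)·[1 + √(1 + 4/(n × 0.25))]² = 55.4, so 56 per arm. Adding 20%: 56 × 1.2 = 67.2, so 68 per arm and **136 in all**. Dividing by 0.8 instead gives 56/0.8 = 70 per arm, 140 in all.
- Fisher's exact test: 136 × 0.8 = 108.8, so 54 evaluable per arm. Exact enumeration at 14% against 39% gives power 79.9%, which is the stated 80% to rounding.

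**3. A second route to 136**

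- At 20% against 45%, the uncorrected formula gives 53.9, so 54 per arm, 108 in all; 108/0.8 = 135, and an even split gives **136**.
- At exactly 20.25% against 45.25% it gives 54.1, so 55 per arm and 138 in all. This route therefore reaches 136 only if the rate is rounded to 20%.

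The printed total fits two different control rates under two different methods.

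**4. Power with 54 evaluable per arm and a 25-point difference (exact enumeration)**

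| Control vs target | Chi-square, uncorrected | Fisher's exact |
|---|---|---|
| 14% vs 39% | 85.4% | 79.9% |
| 20.25% vs 45.25% | 80.5% | 74.5% |
| 21% vs 46% | 80.1% | 74.1% |
| 27% vs 52% | 76.6% | 70.6% |

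The normal-approximation formula for the uncorrected test gives nearly the same values: 84.7%, 79.9%, 79.4% and 76.5%.

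If none of the 68 per arm were lost, power at 20.25% would be about 88% (uncorrected, by formula) or 85% (Fisher).

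**The case against.** Four points can be made for the plan, and each limits what may be concluded.

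- **The rate may be adjusted, not just scaled.** The sentence refers to the trial's own study population, which leaves room for an adjustment that is not shown, and the cited trial's patients and fibrosis scale are not visible here. A reader might infer that 14% contradicts its source. The document supports only that it cannot be derived from what is printed. Still, the article prints both figures and joins them as premise and conclusion, so the missing step is not mere detail left to a fuller document.
- **The sample size is not shown to be wrong.** A reader might infer that 136 patients or the 80% power is an arithmetic error. On the printed inputs both can be reproduced by standard methods, as shown above.
- **The 20% route is a reconstruction.** A reader might infer that 136 was really computed at 20% and that 14% is a misprint. Nothing in the document shows this, and 136 fits 14% as well.
- **The Ethics section is weak support for a higher rate.** It says many patients in such trials "stop drinking or reduce their alcohol consumption, causing spontaneous improvement of their liver disease symptoms". That concerns symptoms, not a 1-point Ishak change, and the 27% also came from a trial, so it may already contain such an effect.

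It is also fair to say that 54 per arm may be pessimistic. Study dropouts include patients who took less than 75% of treatment; some of them may still have a second biopsy and count in the intent-to-treat analysis.

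**Conclusion.** The point stands as a gap in derivation. The 14% is offered as following from 27% over 2 years, time scaling gives about 20% to 21%, and nothing printed bridges the difference. The document also does not show which control rate and method produced 136.

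The consequence depends on the method. If 136 rests on 14% with Fisher's test or a continuity correction, power for a 25-point difference at the time-scaled rate is about 74% to 75% (the Fisher figures) rather than 80%. If an uncorrected chi-square test is used, power stays at about 80%. These figures assume 54 evaluable patients per arm after 20% dropout, and that the cited rate applies to this population with a roughly constant rate of regression over time. The effect on power is thus nil to modest; the effect on the printed control and target rates is about 6 to 7 percentage points.

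**What to change.** In the sample size paragraph of the protocol, and wherever the analysis plan repeats it:

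1. Either replace 14% with the time-scaled rate of about 20% to 21% and the target with about 45% to 46%, or keep 14% and state the adjustment that yields it.
2. Name the test and the dropout formula actually used for the calculation. The 54, 108, 135, 136 sequence should not be presented as the original calculation unless the sponsor confirms it.
3. Restate power for 136 patients (54 evaluable per arm, 25-point difference) at control rates of 14%, 20% and 27%: about 85%, 80% and 77% for the chi-square test, and about 80%, 75% and 71% for Fisher's exact test.

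The cost is one corrected paragraph and no extra patients. The downside is that the stated power may become slightly less favourable. The correction is best made before unblinding, so that it cannot be read as a response to the observed placebo rate.
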